#### Pilot With Care Managers

We will pilot the model the health care researcher will build for Modeling Problem 9 with UWM care managers. As a UWM operational project, we are working on this modeling problem and have access to around 25 UWM care managers. Via announcing in their email lists and personal contact, we will recruit five care managers. We will conduct purposeful sampling to ensure enough variability [94]. All test participants will give consent and have fulfilled UWM’s required training for information security and privacy policy. Participants will receive pseudonyms linking their responses to questions for privacy protection. Upon task completion, each will receive US $200 as compensation for participation.

We will use our previously developed method [15] to automatically explain the model’s prediction results. For each care manager, we will randomly select 20 UWM diabetic adult patients, half of whom the model predicts will incur a cost of more than US $30,000. The care manager is unaware of any of these patients’ outcomes in the next year. For each patient, we will first show the care manager the historical, deidentified patient attributes, then show the prediction result and automatically generated explanations, and finally survey him/her using both open-ended and semistructured questions. The questions will cover whether the prediction result and explanations will change his/her enrollment decision on the patient, their usefulness, and their trustworthiness as shown in Table 2. The questionnaire will contain a text field for gathering comments. We will analyze collected information in a similar way to Aim 1 (d).

**Table 2 table2:** The dependent variable list.

Variable	Description
Impact on enrollment decision	Response to the following question: Will the prediction result and automatically generated explanations change your enrollment decision on the patient?
Usefulness of the prediction result	Response to the following question: How useful is the prediction result? Rating is on a 7-point Likert scale, ranging from “not at all” (1) to “very useful” (7).
Usefulness of the automatically generated explanations	Response to the following question: How useful are the automatically generated explanations? Rating is on a 7-point Likert scale, ranging from “not at all” (1) to “very useful” (7).
Trustworthiness of the prediction result	Response to the following question: In your opinion, how much clinical sense does the prediction result make? Rating is on a 7-point Likert scale, ranging from “not at all” (1) to “completely” (7).
Trustworthiness of the automatically generated explanations	Response to the following question: In your opinion, how much clinical sense do the automatically generated explanations make? Rating is on a 7-point Likert scale, ranging from “not at all” (1) to “completely” (7).

For Modeling Problem 8, medication order and refill information is needed for identifying asthma. The IH dataset contains this because IH has its own health insurance plan. If too much refill information is missed at IH, data from the all-payer claims database [109] will be used. For Modeling Problem 9, in our ongoing UWM operational project, we have used around 30 attributes and approximately 6000 patients to build a basic cost prediction model, which achieved an *R*^2^ close to that of the commercial claims-based model. Since the health care researcher will use many more attributes and patients that should increase model accuracy, we expect the cost prediction model built by him/her to achieve a higher *R*^2^ than the claims-based model.

Although using a constraint to fill the scope gap partially addresses UWM data’s incompleteness, UWM still has incomplete medical data on some of its patients satisfying the constraint. For each such diabetic patient, the dependent variable of the patient’s total allowed cost to UWM is only part of the patient’s total allowed cost to all systems. The patient’s features are computed from incomplete data. Both factors may create difficulty for significantly improving *R*^2^. If this occurs, we will revise the dependent variable to a diabetic patient’s total allowed cost to UWM or reflected by PreManage data. On average, the revised dependent variable is closer to the patient’s total allowed cost to all systems than the original one. Recall that based on UWM patient demographics and PreManage diagnosis data, we will use two models to estimate the allowed cost of each of the patient’s non-UWM inpatient stays and ED visits reflected by PreManage encounter data. We will supplement UWM data with PreManage data to make patient data more complete for computing patient features. This approach of using PreManage data and revising the dependent variable can be adopted to improve the accuracy of predicting future hospital use.

For either new modeling problem, if one health care researcher fails to build a reasonably accurate model, we will recruit another health care researcher.

### Aim 3

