#### Analysis

We will use the accepted inductive approach endorsed by Patton et al [94,98] to do qualitative analysis. We will put the 25 health care researchers’ textual comments into ATLAS.ti Version 8 (ATLAS.ti Scientific Software Development GmbH), a qualitative analysis software tool [99]. The research team will independently highlight quotations related to the issue of using Auto-ML. We will examine quotations, categorize them into precodes, and merge them into categories in multiple iterations. We will synthesize categories to find general themes. Quantitative analyses will include adding the scores in the SUS and presenting every quantitative outcome measure’s descriptive statistics.

### Aim 2

**Overview** Aim 2 involves applying Auto-ML and novel methodology to two new modeling problems crucial for care management allocation, to which our institutions are seeking solutions, and pilot one model with care managers. Both modeling problems use datasets that have repeatedly recorded attributes. We will put the datasets in the OMOP common data model form with its linked standardized terminologies. We will use the same computing environment and recruiting method mentioned in Aim 1 (d). We will recruit two health care researchers not engaged in Aim 1 (d). Each will be randomly given a problem and use Auto-ML to build models for it. Upon task completion, each will receive US $200 as compensation for participation.

#### Modeling Problem 8

Modeling Problem 8 involves the use of vast attributes in modern IH electronic medical records to predict hospital use in asthmatic children in the next year.

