#### Performance Evaluation and Sample Size Justification

For each of the two new modeling problems, we will test the hypothesis that health care researchers are able to use Auto-ML to achieve higher model accuracy than existing approaches. We will regard Aim 2 as partly successful if we accept the hypothesis in only one problem, and completely successful if we accept the hypothesis in both problems.

For Modeling Problem 8, we will compare the accuracies reached by the model built by the health care researcher and the model in Schatz et al [65]. The first model is built using Auto-ML and vast attributes in modern IH electronic medical records. The second model depicting the existing approach was built using a few known risk factors for hospital use in asthma. Using vast attributes can increase prediction accuracy [107]. We will accept the hypothesis when the first model reaches a higher AUC than the second one by at least .05. Existing predictive models for hospital use in asthma usually achieve an AUC far below .8 [63-68]. Assuming these two models’ prediction results have a correlation coefficient of .6 for both classes and performing a two-sided *Z* test at a significance level of .05, a sample size of 561 data instances per class provides 90% power to find a discrepancy of .05 between the two models’ AUCs. The IH data in the 11th year include about 27,000 asthmatic children, offering enough power to test our hypothesis. Using many patients is essential for improving prediction accuracy, although only a small sample size is needed to show statistical significance.

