For Modeling Problem 9, we will compare the accuracies gained by two models. The patient cohort includes those satisfying the chosen constraint. The first model is built by the health care researcher using Auto-ML and clinical and administrative data. The second model depicting the existing approach is a commercial claims-based one available at UWM achieving an *R*^2^ less than 20%. Although the second model was not designed for such use, we will apply it to the patient cohort on whom UWM possibly has incomplete data, which is better than the normal practice of making no predictions. Adding clinical data can increase prediction accuracy [108]. We will accept the hypothesis when the first model reaches a higher *R*^2^ than the second one by at least 5%. Using an *F* test at a significance level of .05 and under the assumption of the existence of 20 features from clinical data in addition to 300 or fewer features used in the second model, a sample size of 443 patients provides 90% power to identify an increase of 5% in *R*^2^ from 20%. Using the second candidate constraint, we estimate that the patient cohort will cover approximately 22% of diabetic adult patients at UWM. The 4th year’s UWM data include approximately 28,000 diabetic adults, offering enough power to test our hypothesis.

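### Aim 2 allows a new researcher or a new outcome after poor accuracy, and no rule says which attempt decides success

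*Protocol article*

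**What the plan says.** Four parts of the Protocol article's Aim 2 bear on this point.

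- **Design (Overview, and Model Information for Problems 8 and 9).** Two researchers who took no part in Aim 1 (d) are recruited, and each is randomly given one problem. Accuracy is estimated on one test year: the 11th for Problem 8 and the 4th for Problem 9.
- **Hypothesis and decision (Performance Evaluation and Sample Size Justification).** For each problem, "we will test the hypothesis that health care researchers are able to use Auto-ML to achieve higher model accuracy than existing approaches". The rule for Problem 8 is: "We will accept the hypothesis when the first model reaches a higher AUC than the second one by at least .05". For Problem 9 it is: "We will accept the hypothesis when the first model reaches a higher *R*^2^ than the second one by at least 5" percent. The overall rule reads: "We will regard Aim 2 as partly successful if we accept the hypothesis in only one problem, and completely successful if we accept the hypothesis". Complete success thus needs acceptance for Problem 8 as well as Problem 9.
- **Replacement of the researcher (closing paragraph of Aim 2, after Pilot With Care Managers).** For either problem, "if one health care researcher fails to build a reasonably accurate model, we will recruit another health care researcher".
- **Change of outcome (same closing text, Problem 9 only).** The protocol notes that incomplete UWM data may make it hard to improve R² significantly. It continues: "If this occurs, we will revise the dependent variable to a diabetic" patient's cost either at UWM or reflected by PreManage data, with non-UWM stays and visits costed by two estimation models. PreManage data would also supplement the features.

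**The concern.** The claim is about what health care researchers can do with the software, and each problem rests on one person. A researcher who cannot build an adequate model is therefore evidence on the claim. Under the replacement rule a second person may then be tried, and nothing says whether the first result still counts. In Problem 9 the condition for changing the outcome is difficulty in improving R², which is the quantity under test. The revised cost is also a different variable, because part of it is estimated by models, so its R² is not the same measure as that of the original outcome.

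Followed as written, these two rules would allow Aim 2 to be called successful because someone eventually succeeded on some version of the outcome. That is weaker than the stated hypothesis, and a reader of the final report could not tell the two apart. The protocol recognises a related hazard in Technique 1 of Aim 1 (a), where it guards against overfitting from repeated use of one validation sample. It describes no such safeguard for the Aim 2 test years.

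**Working it through.** **1. What the stated design figures describe.** Inputs for Problem 9 (Performance Evaluation and Sample Size Justification): R² from 0.20 to 0.25, 20 added features on 300, F test at .05, 90% power.
- f² = 0.05 / (1 − 0.25) = 0.0667; df1 = 20; df2 = N − 320 − 1; noncentrality = N × f².
- The smallest N with power of at least 0.90 is 443 (power 0.9001), which is the plan's own figure.

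For Problem 8 the plan states: "performing a two-sided *Z* test at a significance level of .05, a sample size of 561 data instances per class provides 90% power". The baseline AUC is not given, so 561 cannot be checked exactly. An Obuchowski–McClish type approximation with an assumed baseline AUC of 0.50 to 0.80 gives about 531 to 590, so 561 is plausible. Both figures describe one comparison on one outcome.

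**2. Can chance alone produce success at zero true gain?**
- Problem 9: 22% of 28,000 = 6,160 patients (second candidate constraint). Normal theory, with an assumed correlation of 0.6 between the models: SE = √(4 × 0.2 × 0.8² / 6,160) × √(2 × 0.4) ≈ 0.0082. The 0.05 margin is about 6.1 SE from zero, so the chance is negligible.
- Problem 8: the design implies SE = 0.05 / (1.960 + 1.282) = 0.0154 at 561 per class, and P(difference ≥ .05 | true 0) = 0.0006.

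**3. A true gain just below the margin (Problem 9, true gain 0.04).** For one attempt, 1 − Φ(0.01 / 0.0082) ≈ 0.11. Independent attempts give 0.21 for two and 0.37 for four. With an assumed model correlation of 0.8 these become 0.04, 0.08 and 0.16. In this range the new model is truly better, but by less than the plan requires.

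**4. Selection across researchers.** If one researcher succeeds with probability p, the chance that at least one of k independent researchers succeeds is 1 − (1 − p)^k. The protocol gives neither p nor k. For an assumed p = 0.3:
- k = 2: 1 − 0.7² = 0.51
- k = 3: 1 − 0.7³ = 0.66

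Without a cap this tends to 1 for any p above zero. Positive correlation between attempts would lower these figures.

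**5. The rules side by side.**

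| Rule | Problems | Trigger | Stated limit | Which result decides |
|---|---|---|---|---|
| Replace researcher | 8 and 9 | Model not reasonably accurate (undefined) | None | Not stated |
| Change outcome and features | 9 | R² hard to improve significantly | One named revision | Not stated |

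**The case against.** The strongest reply is that error is controlled where it matters. The plan names .05 tests and adds a margin on large test years, so a useless model would almost never pass. Steps 2 and 3 bear this out, and a reader who inferred that Aim 2 has no error control would be going too far. What is missing is control across attempts and outcome versions.

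Other parts of the reply also stand:
- The trigger for replacement is an undefined accuracy standard, not failure of the hypothesis. It may be meant for unusable models, and the pilot needs a working model for Problem 9. The text does not equate the two.
- Nothing says that a failed attempt is discarded, or that the difficulty with R² would be judged on year 4.
- It is tempting to put Aim 1 (d)'s 60% into step 4, giving 84% for two attempts and 94% for three. That 60% concerns reaching 95% of a gold standard on other problems. Replacements would share software and data, so independence is doubtful. The results would also be chances of success, not of false success.
- The share of researchers who succeed is studied in Aim 1 (d) with 25 people, and Aim 3 takes its probability from there, not from Aim 2.
- The outcome revision is announced in advance, names the new variable and has a substantive reason.

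None of this says which attempt or outcome version decides Aim 2. Nor is this merely detail that a condensed article leaves elsewhere: the replacement and revision rules are stated outright, and so is the success rule they bear on.

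**Conclusion.** The point holds as one of selective success. Aim 2 can be declared partly or completely successful after a change of researcher (either problem) or of outcome and features (Problem 9). Both changes follow poor accuracy, and no rule fixes which result counts. One success after several failures would not support the hypothesis about health care researchers as it is worded.

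The size of the bias cannot be derived from the document. The 0.51 and 0.66 are illustrations resting on an assumed p of 0.3 and independent attempts. The 0.11 to 0.37 for a true R² gain of 0.04 rest on 6,160 patients, an assumed correlation of 0.6 and independent attempts. A reader might infer a large inflation of the type I error; at zero true gain the margin and the size of the test data do not support that.

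**What to change.** State in Aim 2 that:
- the decision for each problem uses the first assigned researcher and the original dependent variable, evaluated once on the held-out year;
- every attempt is reported, with its accuracy and the reason for any replacement;
- results from replacement researchers and from the PreManage-revised outcome are exploratory;
- the accuracy standard that triggers replacement is defined, with a cap on the number of replacements.

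If the revised outcome is to be confirmatory, decide on the revision from years 1 to 3 only, before year 4 is opened, and compare both models on the same outcome. Give both models the same supplemented data where the commercial model allows it; the protocol does not show that it can. Otherwise disclose the unequal inputs.

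The core change costs only wording, and the team keeps the option to replace researchers and try the revised outcome. The confirmatory route for the revised outcome also needs a validation split within years 1 to 3. The downside is that a late success can no longer count as confirmation.

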#### Overview

Aim 3 involves performing simulations to estimate the impact of adopting Auto-ML on US patient outcomes. To determine Auto-ML’s value for future clinical deployment, we will estimate the impact of adopting Auto-ML on US patient outcomes. Trials showed that machine learning helped drop the 30-day mortality rate in ED patients with community-acquired pneumonia (risk ratio≈OR=0.53, as the mortality rate is much less than 1) [2] and cut hospitalization days by 15% in end-stage renal disease patients on dialysis [3]. We will use these two scenarios to demonstrate our simulation method. Our method generalizes to other scenarios and similar software. We will use the same computing environment mentioned in Aim 1 (d). We first discuss the scenario of ED patients with community-acquired pneumonia.

#### Estimate Outcomes

The outcome is 30-day mortality. We will use the latest, deidentified, and publicly available Nationwide Emergency Department Sample (NEDS) database [110], including visit information from approximately 20% of US EDs. Consider the case with Auto-ML. The likelihood, *L*, that an ED can successfully use machine learning for this scenario is equal to *p*_1_× *p*_2_. *p*_1_ is the probability that a health care researcher in the ED can build a high-quality machine learning model for this scenario using Auto-ML. *p*_2_ is the probability that the ED can successfully deploy the model if it can be built. Using Aim 1(d)’s test results on whether health care researchers can use Auto-ML to achieve model accuracy of at least 95% of the gold standard, we will conservatively estimate *p*_1_’s minimum and maximum values (eg, by fitting a normal distribution and using its 2.5 and 97.5 percentile points). Based on his extensive experience with deploying models [2], [name] ([name]) will conservatively estimate *p*_2_’s minimum and maximum values. For each of *p*_1_ and *p*_2_, we will adopt five levels going from the minimum to the maximum value for sensitivity analysis. The middle level is the default one and is used for hypothesis testing.

For each ED in the NEDS database, we will retrieve the annual number of patients with community-acquired pneumonia. We will simulate whether or not the ED can successfully use machine learning for this scenario based on the likelihood, *L*. If success/not success, for each ED patient with community-acquired pneumonia, we will simulate whether the patient will die or not based on the 30-day mortality rate reported in the paper [2] when using/not using machine learning. The overall outcome estimate combines the expected outcomes for all patients and EDs. The patients’ discharge weights in the NEDS database will be used to obtain national estimates from sample data in the database. We will handle the case without Auto-ML similarly by simulating not using machine learning.

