#### Performance Evaluation and Sample Size Justification

We will test the hypothesis that at least 60% of health care researchers can use Auto-ML to achieve model accuracy of at least 95% of the gold standard. When 60% of health care researchers can actually achieve model accuracy of at least 95% of the gold standard, a sample size of 25 health care researchers produces a one-sided 95% lower confidence limit of 42%.

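### Aim 3's example rule for the range of p1 (a fitted normal distribution) suits a proportion from 25 yes/no results poorly when most researchers succeed

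*Protocol article*

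**What the plan says.** Under Aim 3, Estimate Outcomes, the likelihood that an emergency department (ED) can use machine learning is L = p1 × p2. The range of p1 comes from Aim 1(d)'s "test results on whether health care researchers can use Auto-ML to achieve model accuracy of at least 95% of the gold standard", which is a yes/no result for each researcher. The authors will conservatively "estimate *p*_1_’s minimum and maximum values (eg, by fitting a normal distribution and using its 2.5 and 97.5 percentile points". For p1 and p2 alike, "we will adopt five levels going from the minimum to the maximum value for sensitivity analysis". On the default, the section says: "The middle level is the default one and is used for hypothesis testing".

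The number of results is fixed under Aim 1 (d), Performance Evaluation and Sample Size Justification. The hypothesis there reads "We will test the hypothesis that at least 60% of health care researchers can use Auto-ML to achieve model accuracy of at least 95" percent of the gold standard. If 60% of researchers do so, "a sample size of 25 health care researchers produces a one-sided 95% lower confidence limit of 42" percent.

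The article gives no truncation, no transformation and no rule for the case where all 25 succeed. The normal fit is the only method it names for the range, and it is offered as an example.

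**The concern.** A normal distribution is symmetric and unbounded, while p1 is a probability estimated from 25 binary results. Close to 1 its percentile points can pass the boundary, and with no failures its estimated spread is zero. The lower percentile also sits too close to the observed proportion when that proportion is high, which works against the conservative range that the sentence asks for.

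The range of p1 matters because p1 multiplies into L, and L determines for each simulated ED whether machine learning is used. The five p1 levels are the plan's sensitivity analysis on this input. The rule works worst when Auto-ML does well, an outcome that an Aim 1(d) hypothesis of at least 60% leaves open.

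**Working it through.** **Inputs.** n = 25 and the planning proportion 0.60 (15/25) come from Aim 1(d). The 2.5 and 97.5 percentile points, z = ±1.96, come from Aim 3. True success rates other than 60% are assumptions.

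**The plan's own figure.** For 15/25 the one-sided 95% lower limit is:
- exact (Clopper-Pearson), the 5% point of a beta(15, 11) distribution: 0.417, which is 42%
- normal: 0.60 − 1.645 × √(0.60 × 0.40/25) = 0.439
- Wilson: 0.437

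Only the exact method of these three reproduces the stated 42%.

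**The example rule.** Read as a normal distribution for the proportion, the limits are p̂ ± 1.96 × √(p̂(1 − p̂)/25).
- 15/25: 0.60 ± 1.96 × 0.0980 = 0.408 to 0.792
- 22/25: 0.88 ± 1.96 × 0.0650 = 0.753 to 1.007
- 24/25: 0.96 ± 1.96 × 0.0392 = 0.883 to 1.037
- 25/25: standard error 0, so 1.000 to 1.000

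The upper limit exceeds 1 when (1 − p̂) < (1.96²/25) × p̂ and p̂ < 1. That is p̂ > 1/1.1537 = 0.867, so 22, 23 or 24 successes.

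| Successes | Normal | Clopper-Pearson | Wilson | Minimum too high by, vs exact | vs Wilson |
|---|---|---|---|---|---|
| 15 | 0.408–0.792 | 0.387–0.789 | 0.407–0.766 | 0.021 | 0.001 |
| 20 | 0.643–0.957 | 0.593–0.932 | 0.609–0.911 | 0.050 | 0.034 |
| 22 | 0.753–1.007 | 0.688–0.975 | 0.700–0.958 | 0.065 | 0.053 |
| 23 | 0.814–1.026 | 0.740–0.990 | 0.750–0.978 | 0.074 | 0.064 |
| 24 | 0.883–1.037 | 0.796–0.999 | 0.805–0.993 | 0.087 | 0.078 |
| 25 | 1.000–1.000 | 0.863–1.000 | 0.867–1.000 | 0.137 | 0.133 |

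**How often (binomial, n = 25).**

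| Assumed true rate | Maximum above 1 (22–24 successes) | Zero width (25/25) |
|---|---|---|
| 60% | 0.2% | under 0.001% |
| 80% | 23% | 0.4% |
| 85% | 45% | 1.7% |
| 90% | 69% | 7.2% |

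**Reach into the simulation.** With equally spaced levels (an assumption; the article does not state the spacing), 22/25 gives 0.753, 0.817, 0.880, 0.944 and 1.007. Only the top level is inadmissible, and the middle one equals the observed proportion. At the worst overshoot, 24/25, L exceeds 1 only if p2 > 1/1.037 = 0.964.

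**The case against.** The strongest reply is that the normal fit follows an eg. The commitment is to a conservative range, and the authors remain free to choose another method. Their 42% in Aim 1(d) agrees with an exact limit, so they seem to have a suitable method to hand. This stands, and it lowers the priority. It does not remove the point, because the one method named for this range is unsuitable at high success rates.

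It is also true that nothing fails at the planning rate of 60%, and that the larger probabilities rest on true rates that the article does not state.

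A reader might infer more than the article supports:
- *That the rule already fails at 15/25, because a normal fitted to the raw 0/1 values runs from −0.38 to 1.58.* That is not the natural reading of a range for a probability; the distribution of the estimated proportion is.
- *That negative values are a practical risk.* On the proportion reading they need 1 to 3 successes, about one in a million at a true rate of 60%.
- *That the hypothesis test uses an invalid input.* For 1 to 24 successes the middle of the symmetric range is the observed proportion.
- *That no sensitivity analysis is left at 25/25.* Only p1 collapses. Outcome Evaluation and Sample Size Justification also varies p2, the mortality rate and the rate reduction.
- *That all results of 22 or more give a maximum above 1.* At 25/25 the maximum is exactly 1, so the figure at a true rate of 90% is 69%, and 76% only if 25/25 is wrongly counted in.

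Cutting the maximum off at 1 would answer only part of the point: the minimum would stay too high, and 25/25 would still have zero width.

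**Conclusion.** The point holds as a limited one. On the proportion reading, the example rule is sound enough near 60% and deteriorates as success rises. It gives an inadmissible maximum at 22 to 24 successes and no range at all at 25/25, where the default is also 1. From 20 successes up, its minimum is too high by 5 to 14 percentage points against Clopper-Pearson and by 3 to 13 against Wilson, so it is not conservative there.

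The consequence falls mainly on the p1 sensitivity levels. The default used for hypothesis testing is a valid probability except in the degenerate case of all successes (or none). How likely the problem is depends on the unknown true success rate: remote at 60%, more likely than not at 90%. The priority is to consider the change.

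**What to change.** In Aim 3, Estimate Outcomes, replace the normal-distribution example with the two-sided 95% Clopper-Pearson limits of the Aim 1(d) success proportion. These lie within 0 to 1 and have positive width for every result, and they use the exact method that reproduces the 42% in Aim 1(d). Space the five levels equally between the limits and keep the middle level, now the interval midpoint, as the default, in line with the existing text. For 22/25 the levels would be about 0.688, 0.760, 0.831, 0.903 and 0.975.

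The cost is one sentence and no new data. The lower levels become somewhat less favourable. Because the exact interval is asymmetric, so does the default at high success rates: 0.831 in place of 0.88 at 22/25, and 0.931 in place of 1 at 25/25. Using the observed proportion as the default would avoid that shift but would conflict with the middle-level rule.
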